**Methods:**

This analysis will use the National Joint Registry (NJR) elbow dataset and link it with NHS England Hospital Episode Statistics-Admitted Patient Care (HES-APC). It will include eligible patients from the start of the NJR elbow dataset in April 2012 to December 2022. The main objective is to determine the incidence of TER in England. Age-sex standardised rates will be calculated for groups including different ethnicities, and socioeconomic backgrounds, using the mid-year population data provided by the Office for National Statistics. This planned analysis will summarise patient characteristics such as age, sex, body mass index (BMI), hand dominance, American Society of Anaesthesiologists (ASA) grade, indication for TER, socioeconomic status, and patient co-morbidities. It will also examine implant fixation type, classification, brand/type, and changes over time in implant types used in England. Additionally, it will explore the characteristics and volume of the surgeons and hospitals providing primary TER services, including the grade of the primary surgeons, funding source for surgery, and admission type. The analysis will cover the number of procedures performed by surgeons and hospitals annually in England and in each region of England. Finally, the planned analysis will summarise the elective wait time, postoperative length of stay, and any serious adverse events or re-admissions within 30 and 90 days after the TER.

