The HES-APC dataset contains details about inpatient admissions funded by the NHS, including patients in independent hospitals funded by NHS trusts. All patients undergoing TER surgery are admitted to hospital, and their data will be included in the HES-APC. Each NHS trust collects data while the patient receives treatment. The data are usually collated locally by clinical coders using the patient medical records and then submitted to NHS England. Once collated, NHS England processes and assesses the quality of the data and the yearly HES datasets are released for secondary use, including research. HES includes demographic, clinical, and administrative information which can be used to assess the practices and trends of joint replacement surgery. These include information such as co-morbidities, socioeconomic status, length of hospital stay, and ethnicity [19].

The data linkage of HES-APC to the NJR will be performed as part of an existing agreement between the NJR and NHS England. Access to the data is facilitated under NJR permissions. The data linkage will be performed by applying seven linkage methods using a combination of matched NHS numbers, Local patient ID, date of birth, year of birth, gender, and/or matched care provider (Supplementary File 1). Procedures that are matched based any of those linkage methods will be included, but for a procedure to match, the HES-APC hospital episode start date must be the same or before the NJR operation date whilst the NJR operation date must be before or the same as the HES-APC episode end date.

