### Participants

All patients aged 18–100 years old with a primary TER on the NJR elbow dataset from the start of data collection on the 1st of April 2012 to the 31st of December 2022 will be included. Patients are excluded if they did not consent for their data to be used for research purposes, if it is impossible to trace them after surgery, if their ID numbers are invalid, or if the surgery was not performed in England. Several steps will be undertaken to confirm that the included cases are primary TER procedures. This will include (1) ensuring all operative patterns are consistent (2) confirming all reported procedures on the NJR matches the implant components submitted. Unconfirmed procedures and procedures with inconsistent operative patterns (i.e. a sequence of operations where the primary operation is not the first operation in the sequence or where there are multiple primary operations recorded for the same joint) will be excluded from the analyses. The data preparation process and exclusion of non-eligible procedures is summarised in Fig. 1. Eligible NJR procedures will then be linked to the available HES-APC data which includes all patients’ hospital episodes from 23rd of October 1996 to 31st of March 2022. Hospital episodes with invalid ID numbers, implausible dates, unknown discharges dates, and duplicate episodes will be excluded (Fig. 2).

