### Outcome

The primary outcome in this proposed study will be the number and/or the rate of provision of primary TER. Secondary outcomes will include the duration of elective wait and post-operative duration of stay measured in days. Current trends will be described by reporting the outcomes on annual basis.

Serious adverse events (SAE) within 30 days and 90 days from the index TER will also be reported. SAE will be defined as any severe medical complications leading to hospital admission, including pulmonary embolism, myocardial infarction, lower respiratory tract infection, acute kidney injury, urinary tract infection, cerebrovascular events, and all-cause death. SAE will be extracted from the HES-APC data and identified using ICD-10 codes.

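### All-cause death at 30 and 90 days is drawn only from NHS-funded admissions, so the figure undercounts deaths, and the SAE wording leaves index-stay complications unclear

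*Protocol article*

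**What the plan says.** The Outcome section sets the windows: "Serious adverse events (SAE) within 30 days and 90 days from the index TER will also be reported". It gives the definition as "SAE will be defined as any severe medical complications leading to hospital admission", followed by a list of conditions that ends with "cerebrovascular events, and all-cause death". It then names a single source and method for the whole set: "SAE will be extracted from the HES-APC data and identified using ICD-10 codes".

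The Source of data section describes that source: "The HES-APC dataset contains details about inpatient admissions funded by the NHS". NHS-funded patients treated in independent hospitals are included. The same section notes that "All patients undergoing TER surgery are admitted to hospital". The only linkage the article describes is NJR to HES-APC.

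Two other places bear on the point. The Participants section excludes patients "if it is impossible to trace them after surgery", without saying what the tracing provides. The Methods part of the abstract promises a summary of "any serious adverse events or re-admissions within 30 and 90 days after the TER", with no condition that an SAE must lead to admission.

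**The concern.** The label and the source do not match. All-cause death means every death in the window, wherever it happens. A dataset of NHS-funded inpatient admissions has no record of a death at home, in a care home or in a hospice, or in an admission paid for privately. Nor does a diagnosis code by itself show that a patient died.

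The definition also fits its own list badly. Death is not a complication that leads to admission. A complication arising after surgery but before discharge did not lead to an admission either, because the patient was already in hospital.

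At stake is the 30- and 90-day safety description. The Discussion offers the study's outcomes as the reference against which practice after reconfiguration can be compared. A mortality figure that is incomplete but labelled all-cause, or an SAE rate that two analysts could compute differently from the same text, is a weak reference.

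**Working it through.** The article gives no SAE rate, death rate or place-of-death figure, so there is no figure of the plan's to reproduce. The check sets the sections side by side.

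**Deaths**

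1. Outcome: all-cause death is an SAE component, counted from the index operation to 30 and 90 days.
2. Outcome: every SAE comes from HES-APC by ICD-10 code. No exception is made for death.
3. Source of data: HES-APC holds NHS-funded inpatient admissions.
4. From 1 to 3, a death is visible at most when it occurs in an NHS-funded admission.
5. No other section names a mortality source. The exclusion of untraceable patients in Participants hints at follow-up but does not say that it yields deaths or dates of death.
6. The limitations in the Discussion cover how HES records are collected and the lack of clinical and patient-reported outcomes. They do not cover incomplete capture of deaths.

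Let M be the true mortality in the window and f the share of those deaths that occur outside an NHS-funded admission. Even if every death within such an admission is identified, the observed mortality is M × (1 − f), so it cannot exceed M. The documents do not give f. As an assumption only:

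| Assumed f | Share of deaths captured, 1 − f |
|---|---|
| 10% | 90% |
| 50% | 50% |

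Identifying deaths by ICD-10 code could lower capture further, since a diagnosis code does not itself record death.

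**Index-stay complications**

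1. Every TER patient is admitted for the operation (Source of data).
2. An embolism, infarction or stroke after surgery and before discharge lies inside the window, which starts at the index TER (Outcome).
3. It did not lead to an admission, so the literal definition leaves it out.
4. HES-APC is said to include TER patients' admissions, so the index episode's diagnosis codes are available.

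The index-stay issue is therefore one of wording, while the death issue is one of coverage by the source.

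**The case against.** The strongest reply is that the text, read as a whole, points towards counting index-stay events. The window runs from the operation and not from discharge. The abstract names SAEs and re-admissions as separate items. The list includes death, which shows that the phrase about admission is loose. This stands: a reader might infer that index-stay SAEs are lost altogether, but the documents show only that the wording permits that reading.

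A second reply is that in-hospital deaths need not depend on diagnosis codes, because HES-APC also carries administrative information. That is fair, and it means deaths in NHS-funded admissions may be recoverable. It does nothing for deaths elsewhere.

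A third reply is that this is a condensed article and a fuller protocol may name a mortality source. It may, but the article does not merely leave the source open: it states HES-APC for all SAEs, and that statement needs correcting. The lack of a separate definition of re-admission in the Outcome section is different. It is detail an article may leave out, and no fault is claimed there.

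Finally, SAEs are neither the primary outcome (number or rate of TER) nor a named secondary outcome (elective wait and post-operative stay). This also stands and limits the severity.

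**Conclusion.** The point holds at moderate severity. As written, the plan would report as all-cause death a figure that omits deaths outside NHS-funded admissions. The direction is certain, provided some such deaths occur. The size is not known from the documents.

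Two stronger readings are not supported. A reader might try to put a number on the missed deaths, but that needs the count of linked procedures, the 90-day mortality and the share of deaths outside hospital, and the article gives none of these. A reader might also infer that shorter stays after reconfiguration would shift complications from uncounted index stays to counted readmissions and so look like harm. That requires the literal definition, shorter stays, and a later comparison using the definition unadjusted. The article states neither of the last two. Its own analysis is descriptive, and it reports post-operative stay year by year.

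The index-stay part is an ambiguity to be settled before analysis, not a demonstrated loss of events.

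**What to change.** - **Death.** If NJR tracing or a linked death registration supplies a date of death, name it as the source and count deaths from the operation date to 30 and 90 days. If neither does, relabel the component *in-hospital death (NHS-funded admissions)*, identify it from discharge information and not from ICD-10 codes, and add the undercount to the limitations.
- **Separation.** Report death apart from the complications defined by admission.
- **Complications.** Count the listed conditions from the operation date. Report those recorded in the index stay and those leading to readmission as two separate results. State that index-spell coding cannot always tell a new condition from a pre-existing one.

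The relabelling and the definition changes cost a few sentences and some extra tabulation. A date of death may cost more: the article describes an existing agreement for linking NJR to HES-APC and does not show that death registration is covered. Whether the HES-APC extract holds a discharge outcome that identifies death should also be confirmed, since the article does not say.

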### Statistical analyses

Descriptive analysis will be performed for all included variables. Frequencies and proportion will be used to summarize categorical variables. The distribution of continuous variables will be assessed using histograms. It is likely that some of the continuous data, such as surgeons’ and hospitals’ volume, will be skewed, therefore, continuous variables will be reported using the median and interquartile range (IQR). The analyses will include summary of all the included population, stratified analysis for elective and acute trauma population, and analysis for each year from 2012 to 2022. The number of procedures performed by surgeons and hospitals will be summarised for the whole population and for each region in England and the results will also be reported on annual basis.

TER rates for different sexes, age categories, socioeconomic status categories and different ethnic groups will be reported. The rates of primary TER per 100,000 persons will be calculated by dividing the number of procedures in the NJR elbow dataset by the corresponding mid-year population estimates published by the Office for National Statistic (ONS). Sensitivity analysis will be performed using the census estimate from 2021. The population estimates by ethnic group reported by ONS will be used to estimate the rates of TER between different ethnicity groups. Age and sex standardised TER rates for each IMD group will be reported. Statistical analyses will be performed using Stata version 18 (StataCorp LP, USA).

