#### Surgeon and hospital related factors

Most of the surgeon and hospital variables used in this study are not directly reported but will be derived from the available data (Table 3). The NJR includes pseudonymised codes to represent the surgeon who performed the surgery and the hospital where the surgery was performed. This data can be used to calculate the surgeon’s and hospital’s volume. In this project, the annual number of TERs will include all TERs from the 1st of January to the 31st of January of that year. The year 2012 will be excluded from this analysis because data is only available from April 2012.

**Table 3 Tab3:** Surgeon and hospital related variables to be included in the planned study

Variable	Dataset	How will data be presented	Method of measurement
Funding	NJR	Categorical: NHS/Independent sector	Documented directly using a specified list on MDS collection form
Grade of primary surgeon	NJR	Categorical: Consultant/Other	Documented directly using a specified list on MDS collection form
Surgeon volume	NJR	Number of TERs performed by a surgeon per year by surgeons	Derived from pseudonymised codes representing the surgeon in charge of patient care. It represents the number of TERs performed from 1st of January to the 31st of December of each year
Hospital volume	NJR	Number of TERs performed by a hospital per year by surgeons	Derived from pseudonymised codes representing the hospital where TER was performed It represents the number of TERs performed from 1st of January to the 31st of December of each year
Regional volume	NJR	Number of TERs per year by surgeons by region	Derived from the hospital where TER was performed. It represents the number of TERs performed from 1st of January to the 31st of December of each year
Duration of elective wait	HES	Number of days waiting	Derived from the date which it was decided to admit the patient and actual admission date
Post-operative duration of stay	HES	Number of inpatient days following surgery	Derived from the date of surgery and date of discharge
Elective admission type	HES	Categorical: General admission/Day case admission	Documented in patient medical records

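### Annual counts and rates are planned from 2012, a nine-month year, with no part-year adjustment; the 2012 exclusion is worded only for surgeon and hospital volume

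*Protocol article*

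**What the plan says.** Four parts of the protocol article bear on this point.

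- **Participants.** Eligible procedures "from the start of data collection on the 1st of April 2012 to the 31st of December 2022 will be included". The first calendar year therefore lacks January to March.
- **Outcome.** "The primary outcome in this proposed study will be the number and/or the rate of provision of primary TER", and "Current trends will be described by reporting the outcomes on annual basis".
- **Statistical analyses.** The descriptive paragraph lists, with the whole-population summary and the elective and trauma strata, an "analysis for each year from 2012 to 2022". The next paragraph obtains rates per 100,000 by "dividing the number of procedures in the NJR elbow dataset by the corresponding mid-year population estimates". Neither paragraph gives a rule for the incomplete first year.
- **Surgeon and hospital related factors.** After explaining that pseudonymised codes allow surgeon and hospital volume to be calculated, and how the yearly number is counted, the section adds: "The year 2012 will be excluded from this analysis because data is only available from April 2012".

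**The concern.** A mid-year population serves as the denominator of an annual rate because it approximates one year of person-time. Nine months of procedures over that denominator do not give an annual rate. The same problem affects the raw annual count, which is the other form that the primary outcome may take.

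The article gives exactly this reason for leaving 2012 out of the volume analysis. The reason applies equally to annual counts and rates, yet the section that specifies those analyses starts its years at 2012 without comment.

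The abstract makes incidence the main objective, and the Discussion presents the results as the baseline against which practice after reconfiguration will be compared. A first point that is low only because of the registry's start date would make provision appear to have grown at the beginning of that baseline.

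**Working it through.** The article states no 2012 count or rate, so there is no figure of its own to reproduce. The check is direct arithmetic.

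**Inputs**
- Data window: 1 April 2012 to 31 December 2022 (Participants).
- Years analysed: each year from 2012 (Statistical analyses).
- Rate: procedures divided by mid-year population, with no scaling (Statistical analyses).
- Scale only: 258 to 463 replacements per year in England and Wales, 2012 to 2022 (Introduction). These are not England-only counts, and the range may itself include the part year. They serve below only as hypothetical full-year counts.
- Assumption: procedures are spread evenly over the year.

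**Step 1. Share of 2012 observed.** April to December: 30 + 31 + 30 + 31 + 31 + 30 + 31 + 30 + 31 = 275 days. 2012 is a leap year, so the share is 275/366 = 0.751.

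**Step 2. Bias in the 2012 count and rate.** Observed divided by full-year value = 0.751. The shortfall is 1 − 0.751 = 0.249, about 25%.

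**Step 3. Apparent change into 2013.** With constant incidence, the 2013 to 2012 ratio is 366/275 = 1.331, a spurious rise of about 33%.

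**Step 4. Size against chance variation.** A full-year count of 258 would appear as 258 × 0.751 ≈ 194, and 463 as ≈ 348. The Poisson 95% half-width of a single annual count is 1.96/√258 = 12% and 1.96/√463 = 9%, so a 25% shortfall is larger than random error at either end. For the year-to-year ratio:
- 258 against 194: standard error of the log ratio √(1/194 + 1/258) = 0.095. The lower 95% limit is 1.33 × exp(−1.96 × 0.095) ≈ 1.10.
- 463 against 348: standard error √(1/348 + 1/463) = 0.071. The lower limit is ≈ 1.16.

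Even the smallest of these series would therefore show what looks like a real increase.

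**Step 5. Scope of the exclusion.**

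| Reading of the 2012 exclusion | Consequence |
|---|---|
| Volume only (its heading and the lead-in on surgeon and hospital volume) | Annual counts and rates keep 2012 unadjusted, with the bias in steps 2 and 3 |
| All annual counts in the project | Conflicts with the year range that starts in 2012 in Statistical analyses |

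One of the two sections needs a correction on either reading.

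**Step 6. Pooled rate, only if one is calculated.** The window is 3,927 days, and 3,927/365.25 = 10.75 years. Over 11 full mid-year populations the pooled rate would be 10.75/11 = 0.977 of its correct value, about 2.3% too low.

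**The case against.** The strongest reply is that no single sentence says that nine months of procedures will be divided by a full-year population. The 2012 start year stands in the descriptive paragraph, beside medians, interquartile ranges and proportions, and a missing quarter does not scale those down. The rate paragraph names no years. The exclusion is also introduced by a sentence that defines the yearly number of replacements for the project, and Table 3 in that section covers regional as well as surgeon and hospital volume. On this view the authors have seen the problem and solved it, and only the scope is unclear.

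Part of this stands. Age, indication and implant summaries for 2012 are legitimate, and the authors clearly know that the year is incomplete. It does not remove the point. The Outcome section promises the primary outcome by year, the only year range in the Statistical analyses section begins in 2012, and the rate formula has no part-year term. A programmer following the text would produce the low 2012 point.

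A reader might infer three stronger things that the document does not support:

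- **That annual reporting of volumes contradicts the exclusion.** It does not. The sentence on annual volumes names no start year, so volumes can run from 2013.
- **That the overall incidence will be 2.3% too low.** No rate pooled over 11 mid-year populations is specified, so the figure is conditional.
- **That every 2012 summary is distorted.** Only counts, and rates built on them, are affected.

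The study is also descriptive: no test, sample size or decision rule depends on the 2012 value. That limits the harm to the description of trend.

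**Conclusion.** The point holds for annual counts and rates. As written, the Outcome and Statistical analyses sections lead to a 2012 value about 25% too low and, with constant incidence, a spurious rise of about 33% into 2013. The only exclusion of 2012 is worded for volume and, read more widely, conflicts with the stated year range.

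The size rests on an even spread of procedures over the year and on unchanged registry capture from the first month. The article gives no monthly data, and its 93% completeness figure covers the whole period from April 2012 to the start of the live audit, so it says nothing specific about 2012. Seasonality or slow early reporting could move the shortfall from 25%. The mismatch between numerator and denominator would remain.

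**What to change.** In the Statistical analyses section, adopt one of two rules:

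1. Annual counts and rates run from 2013 to 2022, ten full years.
2. 2012 is kept, its mid-year population is multiplied by 275/366, and the point is labelled April–December 2012. A raw 2012 count carries the same label. The scaling raises the unadjusted 2012 rate by a factor of 1.331 and relies on the even-spread assumption.

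Reword the exclusion in the surgeon and hospital section so that its scope agrees with the rule chosen. If any rate is pooled over the whole period, use 10.75 years of person-time instead of 11. Medians and proportions within 2012 need no change.

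The cost is about one sentence and, under the second rule, one denominator factor. No new data are needed. Under the first rule one part-year point is lost from the trend.

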Variable	Dataset	How will data be presented	Method of measurement
Age	NJR	Continuous and age categories	Derived from the date of birth and date of surgery
Sex	NJR	Categorical: Male/Female/Indeterminate	Documented directly using a specified list on MDS collection form
BMI	NJR	Continuous and categorical: Underweight/Normal/Overweight/Obese/Morbidly obese	Documented directly or derived from the weight and height of the patient
Dominant hand	NJR	Categorical: Yes/No/Unknown	Documented directly using a specified list on MDS collection form
ASA	NJR	Categorical: ASA1-ASA5	Documented directly using a specified list on MDS collection form
Indication for surgery	NJR	Categorical: (1) Trauma/Elective (2) Acute trauma/inflammatory/Trauma Sequalae/Osteoarthritis/Other	Documented directly using a specified list on MDS collection form
Socioeconomic status	NJR	Categorical: Indices of multiple deprivation quintiles (2015 version)	Derived from the postcodes and reported as index of deprivation quintiles
Ethnicity	HES	Categorical: Asian, Asian British, or Asian Welsh/Black, Black British, Black Welsh, Caribbean or African/White/Mixed or Multiple ethnic groups/Other ethnic group/Does not apply (students and schoolchildren living away during term-time)	Documented in patient medical records. Classification is based on the ONS group classification 6a [26]
Co-morbidities	HES	(1) Categorical: Acute MI/CHF/PVD/Cerebrovascular Disease/Dementia/COPD/Rheumatoid Disease/Peptic Ulcer/Mild liver disease/Diabetes/Diabetes + Complications/Hemiplegia or Paraplegia/Renal disease/Cancer/Moderate/Severe liver disease/Metastatic Cancer/AIDS/Depression/Anxiety/Osteoporosis (2) Original Charlson Comorbidity Index Hospital (3) Charlson Comorbidity Index Hospital with revised weights	Documented in patient medical records and extracted by admin team at the time of discharge and reported using ICD-10 codes The Charlson Comorbidity Index will be derived from pre-existing condition recorded on HES-APC data using ICD-10 codes

*ASA* American Society of Anaesthesiologists, *BMI*: Body Mass Index, *MI* myocardial infarction, *CHF* congestive heart failure, *PVD* peripheral vascular disease, *COPD* chronic obstructive pulmonary disease

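### The abstract promises age-sex standardised ethnic-group rates but the Methods specify them only for deprivation, and the source of ethnicity covers less than the cohort and the population it is divided by

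*Protocol article*

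**What the plan says.** **Standardisation.** The Methods paragraph of the abstract says: "Age-sex standardised rates will be calculated for groups including different ethnicities, and socioeconomic backgrounds", with Office for National Statistics (ONS) mid-year populations as denominators. Statistical analyses defines the rate per 100,000 as "dividing the number of procedures in the NJR elbow dataset by the corresponding mid-year population estimates". It then treats the two groupings differently. For deprivation: "Age and sex standardised TER rates for each IMD group will be reported". For ethnicity: "The population estimates by ethnic group reported by ONS will be used to estimate the rates of TER between different ethnicity groups", with no mention of age or sex.

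**Where ethnicity comes from.** Table 1 gives HES as the only source. Patient related variables adds a fallback: if ethnicity is missing at the TER admission, it is taken from the patient's other hospital episodes where these are available.

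**What HES-APC covers.** Source of data describes it as holding "inpatient admissions funded by the NHS, including patients in independent hospitals funded by NHS trusts". The same paragraph says: "All patients undergoing TER surgery are admitted to hospital, and their data will be included in the HES-APC". Yet that section also says independent hospitals must submit to the NJR, and Table 3 has an independent-sector category for funding.

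**Dates.** Participants sets NJR inclusion from 1 April 2012 to 31 December 2022, and HES episodes up to 31 March 2022. Under the linkage rule in Source of data, a procedure matches only if its operation date lies between the start and end of a HES episode.

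**The concern.** The rate of TER provision is the primary outcome, and ethnic-group rates are one of its named breakdowns. Two parts of one article describe that breakdown differently, so two analysts could follow it in good faith and publish different ethnic rates. If TER incidence changes with age and ethnic groups differ in age structure, an unstandardised comparison mixes age with ethnicity. It can then show a disparity that is not there, or hide one that is.

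The second problem is a mismatch between numerator and denominator. A patient with no recorded ethnicity cannot be counted in any ethnic group, while the ONS population for that group counts everyone. The Discussion offers these results as the baseline for judging service reconfiguration, and outcomes are to be reported by year. A fall in 2022 ethnic rates caused only by the end of HES data could be read as a real change.

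**Working it through.** The article states no rate, sample size or capture figure for ethnicity, so there is nothing of its own to reproduce. The date gap follows from the documents. The other calculations are illustrations on assumed inputs.

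**1. Date gap (inputs from Participants).**
- NJR window, 1 April 2012 to 31 December 2022: 3,927 days, or 129 months.
- Part covered by HES, to 31 March 2022: 3,652 days, or 120 months.
- Uncovered: 3,927 − 3,652 = 275 days; 275/3,927 = 7.0% (9/129 months = 7.0%).
- All of it falls in 2022: 275/365 = 75% of that year.

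Assuming even accrual, index-episode capture is therefore at most 93% over the whole window and 90/365 = about 25% for 2022, before any recovery through the fallback.

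**2. Further loss from funding and linkage (assumed).** The documents give no share of cases that are NHS-funded and linked. With an assumed share s, overall capture = (3,652/3,927) × s:

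| s | Overall capture | 2022 alone |
|---|---|---|
| 0.98 | 0.911 | 0.242 |
| 0.95 | 0.883 | 0.234 |
| 0.90 | 0.837 | 0.222 |
| 0.85 | 0.790 | 0.210 |

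These too are before the fallback.

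**3. Effect on ratios.** Observed ratio = true ratio × (capture in group A / capture in group B). With a true ratio of 1:
- 0.93 v 0.93 gives 1.00
- 0.85 v 0.93 gives 0.91
- 0.93 v 0.85 gives 1.09

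Incomplete capture lowers each group's rate. It moves the ratio only when capture differs, and in either direction.

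**4. Age confounding (assumed inputs).** Take two age strata with identical age-specific rates in both groups: 0.3 per 100,000 under 65 and 2.5 at 65 and over. The reference group has 20% aged 65 and over.
- Reference: 0.3 × 0.80 + 2.5 × 0.20 = 0.74.
- Comparison group with 10% aged 65 and over: 0.3 × 0.90 + 2.5 × 0.10 = 0.52; unstandardised ratio 0.52/0.74 = 0.70.
- Comparison group with 6%: 0.3 × 0.94 + 2.5 × 0.06 = 0.432; ratio 0.432/0.74 = 0.58.

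The age-standardised ratio is 1.00 in both cases. A second set of assumptions compares the older group with the younger (20% v 5% aged 65 and over), with the older-age rate k times the younger: ratio = (0.80 + 0.20k)/(0.95 + 0.05k). This gives 1.50, 1.93 and 2.46 for k = 5, 10 and 20. Both sets show that age structure alone can create an apparent difference; neither estimates its size in this cohort.

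**5. Does the fallback close the gap?** It is worded for ethnicity missing from the TER admission, which reads as if that admission is in HES. Privately funded cases and operations after March 2022 would have no episode that meets the date rule. If such patients can still be traced to earlier HES records, which go back to October 1996, some ethnicity could be recovered. The article does not say whether procedures without a matching episode may use it.

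**The case against.** The strongest reply is that Statistical analyses never calls the ethnic rates crude. Its sentence names a denominator source, which standardisation would also need, and the abstract says outright that these rates will be standardised. On that view the Methods sentence is merely incomplete, in an article that condenses a fuller protocol. This stands in part: a reader might infer that the plan has decided on crude ethnic rates, and the text does not show that. But the section defines a rate as procedures over population and names only IMD for standardisation. The two statements disagree, and the disagreement is on the page rather than a detail left to another document.

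A reader might also infer that ethnic comparisons will be understated. That does not follow: the level of the rates falls, but a ratio is unchanged under equal capture and can move either way under unequal capture. Nor is it established that the ethnic numerator holds only linked, NHS-funded cases, because the fallback may recover others.

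It is also fair to say that the study is descriptive, with no stated test on ethnicity, and that overall, age, sex and IMD rates use NJR variables and are untouched. The sixth ethnic category, "Does not apply (students and schoolchildren living away during term-time", is odd for patients, but it is attributed to the cited ONS classification and an empty category biases nothing. It is a minor point.

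**Conclusion.** The point holds in a limited form. The abstract and Statistical analyses disagree on whether ethnic-group rates are age-sex standardised, and the latter as written leaves them open to confounding by age and sex. The direction and size of that confounding cannot be derived from the documents.

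The statement that all TER patients' data will be in HES-APC is inconsistent with the article's own account of that dataset, with its funding variable and with its dates. The part that can be sized from the documents is 7.0% of the inclusion window with no index HES episode, concentrated in 9 of the 12 months of 2022. Reading this as a loss of cases assumes even accrual and no recovery through the fallback. Any further loss from private funding or failed linkage is unknown. The consequence is ethnic rates that are too low in level, most of all for 2022. Bias in comparisons between groups would need capture to differ by group, on which the documents give no information.

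**What to change.** 1. In Statistical analyses, state that ethnic-group rates will be directly age-sex standardised in the same way as IMD rates, using population counts by age, sex and ethnic group, and that years will be pooled if cells are small.
2. Restrict both numerator and person-time of the ethnic rates to the period HES covers, 1 April 2012 to 31 March 2022. This is 120 months, with 2022 contributing three months of person-time.
3. Report the number with unknown or unlinked ethnicity by year and by funding, and say whether the fallback applies to procedures without a matching HES episode.
4. Correct the sentence in Source of data so that it agrees with the NHS-funded scope of HES-APC and its end date.

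The cost is minor analysis work and a few sentences. The downside is that annual ethnic rates may have to be pooled and would stop before the end of 2022. Overall, age, sex and IMD rates need not change.
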